### 2.3. Sample Size Calculation

The sample size calculation based on logistic regression analysis approximately require 20 variables, regarded as risk factors for SI-ARDS, which are selected from radiomic features based on a previous study [20]. Meanwhile, the number of sepsis patients should be 5–10 times the number of risk factors. Considering a 25–50% occurrence rate of ARDS in sepsis patients [21,22], we calculate a minimum sample size of 160 patients for the discovering group.

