## 2. Materials and Methods

### 2.1. Study Design

The study was registered with ClinicalTrials.gov (NCT04541264, https://clinicaltrials.gov/show/NCT04541264) on 9 September 2020. In this double-center, ambispective, observational study, we will collect chest CT and clinical information of patients with sepsis and septic shock treated in our hospital (Sun Yat-sen Memorial Hospital, Sun Yat-sen University) and Shenshan Medical Center, Memorial Hospital of Sun Yat-sen University (from 1 May 2015 to 30 May 2022). For the final analysis, 400 patients will be enrolled according to the TRIPOD guideline [19]. Among the 400 patients, 200 will be retrospectively recruited from our hospital from May 2015 to August 2020, 100 patients will be prospectively recruited from our hospital from August 2020 to May 2022, and the other 100 patients will be prospectively recruited from Shenshan Medical Center, Memorial Hospital of Sun Yat-sen University from August 2020 to May 2022. One hundred-sixty patients of the retrospective cohort will be selected as a discovering group to reconstruct the model, and 40 patients of the retrospective cohort will be selected as a testing group for internal validation. Additionally, 200 patients of the prospective cohort will be selected as a validating group for external validation. Follow-up of the relevant patients will be conducted until April 2023. This study was approved on 19 August 2020 by the Ethics Committee of Sun Yat-sen Memorial Hospital, Sun Yat-sen University, Guangzhou, China. Figure 1 shows the flow chart of the study protocol.

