We intend to employ modified ResNeSt [24], DenseNet [25] and EfficientNet [26] models to train a robust model. All networks will use 3D convolution, ReLU/LeakyReLU nonlinear activation function and batch normalization. For the entire CT image and the outlined region of interest, we will train two convolutional neural networks to extract features. For the ROI, we will randomly sample the voxels containing 80% of the ROI from the entire CT image to generate an image. We will perform five-fold cross-validation on the training set in model training phase, and use random rotation, translation and transposition data enhancement strategies to increase the data and reduce the imbalance between classes. Additionally, the network will adopt the cross-entropy loss as a loss function, Xavier as initialized parameter and stochastic average gradient descent as optimizer. In the last fully connected layer of the network, we will modify the corresponding structure by adding pre-processed clinical variables and other data, and finally predicted whether ARDS might occur.

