### 2.7. Statistical Analysis

Continuous variables between two groups will be compared by T test or Wilcoxon rank sum test, whereas categorical variables will be compared by χ^2^ test. Univariate and multivariate logistic regression will predict occurrence of ARDS, using variables that selected by consensus of variable importance ranking by random forest [28] and least absolute shrinkage and selector operation (LASSO) regression techniques [29]. With the selected clinical and radiomics features, we will develop two versions of the ARDS prediction model, using logistic regression (LR) and support vector machine (SVM). Then a prognostic model will be built for prediction of individual and classification of severe level. ROC curves will determine the optimal cut-off point for models, and patients will be divided into high-risk and low-risk groups. VFD, RFFD and 28-day mortality will be screened indicators with LASSO-COX and RFE-SVM algorithm. Thereafter, these will be estimated using the Kaplan–Meier method. All these algorithm performances will be assessed using the AUC and *p*-values less than 0.05 will be considered statistically significant. After these main analyses, other subgroups will be carried out as following: septic shock vs. non-septic shock, and pulmonary sepsis vs. non-pulmonary sepsis. Statistical analysis will be performed using the R programming language, including its packages.

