Recently, artificial intelligence-based radiomics applied in predicting patients who are at risk of developing immunotherapy-induced pneumonitis and radiation pneumonitis have shown promising results [20,38]. Based on these findings, future studies could focus on comparing predictive values of different imaging approaches, such as CT, ultrasound and bronchoscopy combined with artificial intelligence technology. In this ambispective cohort study, we developed and validated a novel model incorporating radiomic signatures and clinical signatures to provide an easy-to-use and individualized prediction of SI-ARDS occurrence and severe degree in patients at early stage. Moreover, research has indicated that immune microenvironment abnormalities play a critical role in SI-ARDS [39,40], revealing that disturbances of neutrophil migration and neutrophil apoptosis caused neutrophil accumulation in the lung tissues, resulting in lung injury. We considered and initially explored correlation between radiomic features and immune-associated inflammatory indicators.

This study has several limitations. First, there are intrinsic limitations and possible patient selection bias in this observational and partly retrospective cohort study. Since the majority of sepsis patients first receive a chest X-ray, those with a relatively high risk of ARDS would be referred for chest CT and those with severe septic shock would receive bedside chest radiograph. However, a subgroup analysis will be performed by comparing mild sepsis group alone (removing the septic shock subgroup) with the pulmonary and non-pulmonary sepsis group. Second, the follow-up duration is relatively short. However, this period is quite adequate for consideration of the early primary outcome of SI-ARDS. A third limitation is the relatively small sample size and that high-dimensional extracted radiomics features may result in model overfitting. Therefore, these available data still remain inconclusive and need to be further validated in future multicenter prospective studies.

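### Section 2.3's minimum of 160 counts patients where a logistic model needs ARDS events, and it does not follow from the stated inputs; with 20 variables it leaves 2–4 events per variable

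*Protocol article*

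**What the plan says.** Section 2.3 ties the sample size to logistic regression: "The sample size calculation based on logistic regression analysis approximately require 20 variables, regarded as risk factors for SI-ARDS". The rule that follows is expressed in patients: "Meanwhile, the number of sepsis patients should be 5–10 times the number of risk factors". The event rate comes next, "Considering a 25–50% occurrence rate of ARDS in sepsis patients", and the paragraph ends with the result: "we calculate a minimum sample size of 160 patients for the discovering group". It gives no multiplier within 5–10 and does not say how the ARDS rate enters.

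Section 2.1 uses the same number as the model-building set: "One hundred-sixty patients of the retrospective cohort will be selected as a discovering group to reconstruct the model". These come from 200 retrospective patients, and the other 40 form the internal test group. Section 2.7 confirms a binary outcome: "Univariate and multivariate logistic regression will predict occurrence of ARDS". The variables are chosen by agreement of random forest and LASSO, and logistic and support-vector versions of the model are then built. The Discussion concedes that the sample is fairly small and that "high-dimensional extracted radiomics features may result in model overfitting".

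**The concern.** In a binary logistic model the information is limited by the smaller outcome class, so a per-variable rule of thumb is normally applied to events. Section 2.3 applies it to all sepsis patients. The ARDS rate it mentions has no role in a patient count, whereas an event count cannot be done without it. The paragraph therefore brings in the rate but does not visibly use it.

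This is the only sample size justification the article gives for the set on which the model is built. A reader will take 160 as evidence that the logistic model is adequately supported. If it is not, the performance seen in the discovering group will be too favourable, predicted risks will be too extreme, and discrimination will fall in the prospective cohort.

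**Working it through.** **Inputs.** About 20 variables, a multiplier of 5–10, an ARDS rate of 25–50% and a stated minimum of 160 (all Section 2.3). The discovering group is 160 of 200 retrospective patients (Section 2.1).

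**Step 1. Try to reproduce 160 with the rule as written (patients).** N = k × 20.
- k = 5: 100
- k = 7.5: 150
- k = 10: 200

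The range is 100–200 and its minimum is 100. The figure 160 equals 8 × 20, so it is inside the range, but a multiplier of 8 is stated nowhere and the ARDS rate is unused.

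**Step 2. Apply the same multipliers to ARDS events.** N = k × 20 / rate.

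| Events per variable | Events needed | N at 50% | N at 25% |
|---|---|---|---|
| 5 | 100 | 100 / 0.50 = 200 | 100 / 0.25 = 400 |
| 10 | 200 | 200 / 0.50 = 400 | 200 / 0.25 = 800 |

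The range is 200–800, and no combination gives 160.

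**Step 3. Other routes to 160.**
- 5 × 20 / (1 − 0.375) = 160. This needs an unstated midpoint rate and counts patients *without* ARDS.
- 0.8 × 200 = 160, an 80/20 split of the retrospective cohort.

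The article states neither route.

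**Step 4. What 160 patients provide.** Events = 160 × rate; events per variable = events / 20.
- 25%: 40 events, 40 / 20 = 2.0
- 37.5%: 60 events, 60 / 20 = 3.0
- 50%: 80 events, 80 / 20 = 4.0

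Section 2.5 plans cross-validation for the networks: "We will perform five-fold cross-validation on the training set in model training phase". If the logistic model were trained in the same folds, each would hold 160 × 4/5 = 128 patients, with 32–64 events, or 1.6–3.2 per variable. The 20 variables are themselves the product of selection from a larger radiomic pool. Events per candidate feature are therefore lower, but the article does not give the size of the pool, so no ratio can be computed.

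**Step 5. Illustration of the consequence.** These settings are assumptions, not figures from the article: n = 160, 20 independent normal predictors with equal coefficients, linear-predictor SD 1.25, 300 replicates.

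| Fit | Apparent AUC | AUC in new patients | Calibration slope |
|---|---|---|---|
| Unpenalised, 20 predictors | 0.84–0.85 | 0.72–0.73 | about 0.46–0.53 |
| Ridge, same 20 predictors | – | about 0.72–0.73 | about 0.84–1.2, depending on penalty |

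The best achievable AUC in this setting is about 0.78–0.79. Penalisation leaves discrimination about unchanged and largely repairs calibration. The true signal is unknown, so this shows the direction and rough size only.

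**The case against.** Several points on the other side have force.

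- **160 does not break the rule as written.** A reader might infer that the study fails its own 5–10 criterion because 2–4 is below 5. The document does not support that: its criterion is in patients, and 160 gives 8 per variable. Setting 2–4 events against that threshold mixes units. What stands is that the unit is wrong for this model and the figure is underived.
- **The final model is not fixed.** A reader might infer that an unpenalised 20-variable logistic regression will be fitted. Section 2.3 gives 20 as an approximate planning number. Section 2.7 states neither how many variables will be retained nor whether coefficients will be refitted without a penalty. The 2–4 figure is therefore conditional on 20 variables being used.
- **A condensed article may omit a derivation.** This is fair as regards the missing multiplier. It does not cover the unit, which the article states explicitly.
- **The risk is disclosed and will be tested.** The Discussion names overfitting and calls for further multicentre validation. A 40-patient internal test and a 200-patient prospective validation are planned, so the development AUC will not stand alone. This limits the harm but leaves Section 2.3 uncorrected.

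A reader might also infer that the number of predictors should be capped at observed events divided by 5 (8 at 25% ARDS, 16 at 50%). The article sets no such events rule, and the illustration speaks against the cap. Keeping the 8 strongest of the 20 by data-driven selection lowers new-patient AUC to about 0.67 with the slope still near 0.5. Keeping 16 gives about 0.72 and 0.49–0.54, no real gain.

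**Conclusion.** The point holds in a limited form. Section 2.3 counts patients where a binary logistic model calls for ARDS events, and 160 does not follow from its inputs on either count (100–200 by patients, 200–800 patients by events). The group will contain 40–80 ARDS cases, or 2–4 per variable for 20 variables, with fewer per candidate feature.

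This rests on the article's own 25–50% rate and 20 variables, and on the general principle that such rules count the smaller outcome class. The AUC and slope figures rest on assumed simulation settings. The correction should be made, but given the Discussion's caveat and the planned prospective validation, the error does not invalidate the design.

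**What to change.** Keep enrolment as it is and make three changes.

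1. In Section 2.3, state that 160 patients are expected to give 40–80 ARDS events at a rate of 25–50%, which is 2–4 events per variable if 20 variables are used, and that events per candidate feature before selection are fewer.
2. Delete the claim that 160 is a calculated minimum.
3. In Section 2.7, specify that the logistic version of the model keeps its penalised (LASSO or ridge) coefficients and is not refitted without a penalty after selection.

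The cost is wording plus one modelling rule, with no extra patients. The stated adequacy becomes less favourable. Penalised coefficients also come without conventional p-values, so Section 2.7's 0.05 threshold could not be applied to them in the usual way.

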### 2.4. Data Collection

All clinical data will be collected by investigators and trained personnel. Each participant’s data will be filled in electronic case report forms (CRF) and stored online using research electronic data capture (REDCap) [23]. The CRF is designed to collect the necessary information based on this study protocol. The detailed contents of CRF contain four main parts: (1) demographics and chronic disease history (including age, gender, smoking status, hypertension, diabetes mellitus, chronic lung disease and coronary heart disease), (2) laboratory tests and imaging examination (including routine blood, routine biochemistry, coagulation function, arterial blood gas analysis, blood culture, sputum culture, and ID of chest CT), (3) treatment process (including source of infection, anti-infection therapy, ventilator use or not, and type and dose of vasopressor therapy), (4) outcomes (intensive care unit (ICU) stay or not, length of ICU stay, total length of hospital stay, and in-hospital death).

### 2.5. Work-Flow of Radiomics Analysis

To feed the data for the model training, we will initially perform the data pre-processing for CT images and clinical features. Since CT-scanning of an individual utilizes different equipment and parameter settings, inhomogeneities in voxel spacing of the CT DICOM image is very common. To facilitate the data processing of the convolutional neural networks, we will count each grid of pixels with x × y × z pixel dimensions. Then, taking the median of each direction as the standard, we will use bilinear interpolation in the X and Y directions and nearest neighbor interpolation in the Z direction. Based on the theory that organs quantified by CT image require intensity values, the same intensity value represents the same change when scanning the same organ. We will select the lung window settings as width 1500 HU and level −500 HU and take 5–95% of the pixel values to make the intensity value more easily fall in the range for which the convolutional neural network is working. To further enhance the accuracy, we intend to manually outline the region of interest (ROI) to reduce the input of useless information. For the clinical information form, we will first deal with missing values and outliers with methods such as filling in 0, filling in the average value or eliminating them. We will then normalize all numerical variables for input into the neural network model. The workflow of data pre-processing can be seen in Figure 2.

We intend to employ modified ResNeSt [24], DenseNet [25] and EfficientNet [26] models to train a robust model. All networks will use 3D convolution, ReLU/LeakyReLU nonlinear activation function and batch normalization. For the entire CT image and the outlined region of interest, we will train two convolutional neural networks to extract features. For the ROI, we will randomly sample the voxels containing 80% of the ROI from the entire CT image to generate an image. We will perform five-fold cross-validation on the training set in model training phase, and use random rotation, translation and transposition data enhancement strategies to increase the data and reduce the imbalance between classes. Additionally, the network will adopt the cross-entropy loss as a loss function, Xavier as initialized parameter and stochastic average gradient descent as optimizer. In the last fully connected layer of the network, we will modify the corresponding structure by adding pre-processed clinical variables and other data, and finally predicted whether ARDS might occur.

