### 2.6. Outcome Measures

In this study, the primary outcome measure will be occurrence of ARDS, which is defined as pulmonary or nonpulmonary sepsis that had progressed into ARDS.

Secondary outcome measures are as follows:

(1)Grade of pulmonary damage: patients will be classified as mild (200 <  PaO2/FiO2 ≤ 300 mmHg), moderate (100 < PaO2/FiO2 ≤ 200 mmHg), or severe (PaO2/FiO2  ≤  100 mmHg) at the moment of diagnosis of ARDS [2];(2)Ventilator-free days, VFD: defined as the number of days between successful weaning from mechanical ventilation and day 28 after ICU admission;(3)Respiratory organ failure-free days, RFFD: defined as the number of days between a day without evidence of respiratory organ failure [27];(4)28-day mortality: all-cause mortality within 28 days following enrolment.

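### One menu of zero-fill, mean-fill or elimination covers both missing values and outliers, with nothing confining zero to variables where it is valid or elimination to data errors

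*Protocol article*

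**What the plan says.** Section 2.5 (Work-Flow of Radiomics Analysis) states for the clinical form: "we will first deal with missing values and outliers with methods such as filling in 0, filling in the average value or eliminating them". The next step is: "We will then normalize all numerical variables for input into the neural network model". The processed values then enter the network's last fully connected layer, described as "adding pre-processed clinical variables and other data, and finally predicted whether ARDS might occur".

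According to section 2.4 (Data Collection), the form includes "routine blood, routine biochemistry, coagulation function, arterial blood gas analysis". It also holds fields of another kind: sex, smoking, comorbidities, ventilator use, and type and dose of vasopressor.

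The article does not define an outlier. It does not say which option applies to which variable, or whether elimination means a value, a variable or a patient.

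**The concern.** The issue is the methods the protocol names, not detail left to a later analysis plan. There are three problems.

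- **Zero-fill.** Zero is not a physiologically possible result for blood-gas tensions and most laboratory tests. On an oxygenation scale where lower is worse, and where section 2.6 sets the worst class as "severe (PaO2/FiO2 ≤ 100 mmHg", a filled 0 would read as worse than any real patient. Because normalisation follows filling, the zeros also enter the mean and SD used to scale everyone else.
- **One menu for two problems.** A missing value is unknown. An outlier is known and may be correct, and in sepsis it may carry the signal.
- **Undefined elimination.** The choice stays open until the data have been seen, and on one reading it reduces a discovery set that is already at its stated minimum.

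At stake are the clinical inputs to the model for the primary outcome, and how well that model transfers from the retrospective discovering group to the prospective validating group.

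**Working it through.** The protocol gives no figure for this step, so there is none to reproduce. From the documents: discovery set 160, about 20 variables, ARDS rate 25–50% (section 2.3), and filling before normalising (section 2.5). Everything else below is assumed.

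**1. Effect of zero-fill on scaling.** Assume a PaO2/FiO2-like marker with mean 400 and SD 60, of which a fraction p is filled with 0.
- Mean = (1−p)·400.
- Variance = (1−p)(60² + 400²) − mean².
- Filled patients sit at z = −mean/SD.

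| p | mean | SD | z of filled patients | SD if mean-filled, 60·√(1−p) |
|---|---|---|---|---|
| 5% | 380 | 105 | −3.6 | 58.5 |
| 10% | 360 | 133 | −2.7 | 56.9 |
| 20% | 320 | 169 | −1.9 | 53.7 |

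Example at 10%: 0.9 × 163,600 − 360² = 17,640, and its square root is 132.8.

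**2. Effect of zero-fill on single-marker AUC.** Assume a normal marker 1 SD lower in ARDS. The complete-data AUC is A = Φ(1/√2) = 0.760. A filled 0 ranks below every observed value. With fractions p₁ (ARDS) and p₀ (no ARDS) filled,

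AUC = (1−p₁)(1−p₀)A + p₁(1−p₀) + p₁p₀/2.

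- Missing at random, p₁ = p₀ = 10/20/30%: 0.711/0.667/0.628. For 10%: 0.81 × 0.760 + 0.09 + 0.005.
- Missing in 3/14%, 6/28% and 9/42% of ARDS/non-ARDS patients: 0.66, 0.57 and 0.47.
- Missing three times as often in non-cases, 10% overall: 0.68 (ARDS rate 25%) or 0.66 (rate 50%). At 20% overall: 0.60 or 0.56.

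**3. Effect of mean-fill.** Assume an ARDS rate of 35% and values missing at random. The overall mean then lies 0.35 SD below the non-ARDS mean and 0.65 SD above the ARDS mean.

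AUC = (1−p)²A + p(1−p)[Φ(0.65) + Φ(0.35)] + p²/2.

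This gives 0.745/0.727/0.707 at 10/20/30%. The values stay possible; the cost is shrunken variance and a weaker association.

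**4. Elimination, if patients are dropped.** With a fraction q of values missing or outlying per variable, independent over 20 variables, 160·(1−q)²⁰ patients remain.

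| q | patients left | ARDS events at 25–50% |
|---|---|---|
| 0% | 160 | 40–80 |
| 1% | 131 | 33–65 |
| 2% | 107 | 27–53 |
| 5% | 57 | 14–29 |

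**5. Who is lost if outliers are removed.** These are simulations with 400,000 patients.
- Right-skewed (lognormal) marker, higher in cases, 1.5 × IQR rule: about 5% removed. At a 25% ARDS rate, 13% of cases are lost against 2.5% of non-cases. At 50%, 8.6% against 1.4%.
- Symmetric marker, 2-SD rule: cases make up 43% of those removed at a 25% rate, and 50% at a 50% rate. The latter is no preferential loss.

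**The case against.** The strongest reply is that the sentence lists examples joined by an or, so it does not prescribe zero-fill for any particular variable. That stands, and several stronger readings fail with it.

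- A reader might infer that the plan will put impossible values into the model. It permits this but does not say so. A filled mean is not impossible, and for binary fields or vasopressor dose 0 can be the true value.
- A reader might infer that the sickest patients will be removed. The pronoun after eliminating refers to missing values and outliers together, so values, variables or patients could be meant. With no outlier rule, who is lost cannot be known, and step 5 shows that preferential loss depends on the marker's shape.
- A reader might infer that the model will learn who was tested, because tests are ordered for cause and differently by hospital. The article does not say this about laboratory tests; its selection remark in the Discussion concerns imaging. Outcome-dependent missingness is therefore an assumption.
- A reader might infer that severity grades will be corrupted. The section 2.6 grading is a secondary outcome, and nothing says it will be filled. PaO2/FiO2 serves here only as a familiar scale; since eligibility and ARDS diagnosis both use it, it may seldom be missing.
- A reader might cite a reversed association. It appears only at 42% against 9% missing. With a threefold ratio and up to 20% filled, the AUC stays at 0.56 or above.

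All the AUCs are for one marker; the effect on the combined CT and clinical model is not shown. What survives is that the protocol itself names these methods, for both problems, without limits.

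**Conclusion.** The point holds as a poorly fixed method and should be corrected; it does not show that the analysis will fail. The text settles three things: missing values and outliers share one menu, filling comes before normalisation, and neither zero-fill nor elimination is restricted. For laboratory and blood-gas variables zero-fill is wrong at any rate of missingness, because the value cannot occur.

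Its size rests on assumed rates: a loss of 0.05 to 0.13 in single-marker AUC for 10–30% filled at random (0.76 to 0.71–0.63), more if missingness depends on outcome, against 0.015 to 0.05 for mean-fill. A discovery set below "we calculate a minimum sample size of 160 patients for the discovering group" follows only if elimination means patients. Preferential loss of severe cases is a possibility for right-skewed markers, not a stated or certain result.

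**What to change.** Replace the sentence in section 2.5 with separate rules.

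- **Missing values.** Do not fill continuous laboratory or blood-gas variables with 0. Use 0 only where it is a true value, such as no vasopressor. Replace constant filling of continuous predictors with model-based imputation, for example chained equations. A single imputation model is acceptable for the network.
- **Fitting.** Estimate imputation and scaling in the training folds only, and apply them unchanged to the testing and validating groups.
- **Outliers.** Correct only verified entry errors. Keep genuine extremes, transformed or winsorised, and exclude no patient for an extreme value.
- **Sensitivity.** Report complete-case results alongside.

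The cost is a paragraph of text, extra coding and some repeated model fitting. That fitting is not trivial with three architectures, two image inputs and five folds, which is why a single imputation model is a reasonable compromise there. No new data are needed.

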## Abstract

**Background:** Sepsis commonly causes acute respiratory distress syndrome (ARDS), and ARDS contributes to poor prognosis in sepsis patients. Early prediction of ARDS for sepsis patients remains a clinical challenge. This study aims to develop and validate chest computed tomography (CT) radiomic-based signatures for early prediction of ARDS and assessment of individual severity in sepsis patients. **Methods:** In this ambispective observational cohort study, a deep learning model, a sepsis-induced acute respiratory distress syndrome (SI-ARDS) prediction neural network, will be developed to extract radiomics features of chest CT from sepsis patients. The datasets will be collected from these retrospective and prospective cohorts, including 400 patients diagnosed with sepsis-3 definition during a period from 1 May 2015 to 30 May 2022. 160 patients of the retrospective cohort will be selected as a discovering group to reconstruct the model and 40 patients of the retrospective cohort will be selected as a testing group for internal validation. Additionally, 200 patients of the prospective cohort from two hospitals will be selected as a validating group for external validation. Data pertaining to chest CT, clinical information, immune-associated inflammatory indicators and follow-up will be collected. The primary outcome is to develop and validate the model, predicting in-hospital incidence of SI-ARDS. Finally, model performance will be evaluated using the area under the curve (AUC) of receiver operating characteristic (ROC), sensitivity and specificity, using internal and external validations. **Discussion:** Present studies reveal that early identification and classification of the SI-ARDS is essential to improve prognosis and disease management. Chest CT has been sought as a useful diagnostic tool to identify ARDS. However, when characteristic imaging findings were clearly presented, delays in diagnosis and treatment were impossible to avoid. In this ambispective cohort study, we hope to develop a novel model incorporating radiomic signatures and clinical signatures to provide an easy-to-use and individualized prediction of SI-ARDS occurrence and severe degree in patients at early stage.

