### 2.2. Cohort Descriptions and Definitions

This study will recruit 200 patients in a developing group and 200 patients in a validating group from two hospitals. Patients’ age above 18 years diagnosed as sepsis or septic shock will be screened for eligibility. SI-ARDS is defined by sequential occurrence of the sepsis-3 consensus criteria for sepsis [7] and the Berlin definition for ARDS [2]. Exclusion criteria are (1) admission stay <24 h, (2) patients with end-stage lung disease or long-term oxygen therapy, (3) patients with sepsis or septic shock whose oxygenation index (OI, arterial oxygen tension/inspired oxygen fraction [PaO2/FIO2]) ≤300 mmHg before admission, (4) a history of lung transplantation and chronic obstructive pulmonary disease, and (5) cancer patients who have/have not received chemotherapy. Since sepsis and ARDS are not easy to diagnose, two doctors will separately perform patient inclusion/exclusion criteria, extract the data, and assess the data quality. Any discrepancies will be resolved by consensus, and if necessary, a third professor can be consulted.

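### Model inputs are not tied to a prediction time, so data from after ARDS onset, including the blood gases that define ARDS, can enter its prediction

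*Protocol article*

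**What the plan says.** - **Inputs to the network (section 2.5).** Pre-processing of the clinical data begins: "For the clinical information form, we will first deal with missing values and outliers". It continues: "We will then normalize all numerical variables for input into the neural network model". At the last fully connected layer the network is changed by "adding pre-processed clinical variables and other data, and finally predicted whether ARDS might occur".
- **What the form holds (section 2.4).** The case report form is the only form described. Its laboratory part includes "coagulation function, arterial blood gas analysis, blood culture, sputum culture, and ID of chest CT". Its treatment part includes "ventilator use or not, and type and dose of vasopressor therapy". Its fourth part, labelled as outcomes, includes "length of ICU stay, total length of hospital stay, and in-hospital death". No item carries a measurement time.
- **Inputs to the other models (section 2.7).** Variables for the logistic regression and support vector machine models are chosen by agreement between random forest ranking and LASSO. No time criterion is given.
- **What is predicted.** The Abstract gives the aim as "predicting in-hospital incidence of SI-ARDS", at an early stage. Section 2.2 defines the outcome as sepsis followed by Berlin ARDS. Section 2.6 grades ARDS by PaO2/FiO2, with every grade at or below 300 mmHg.

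**The concern.** A model for early prediction may use only what is known when the prediction is made. This plan names no such moment. A blood gas without a time may be the admission value, or it may be the value on which ARDS was diagnosed. Ventilator use and vasopressor dose, if recorded over the whole stay, may follow from ARDS and not precede it.

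The AUC, sensitivity and specificity for the primary outcome are at stake. A model that has seen the diagnostic oxygenation value looks accurate but cannot be used before diagnosis. A strong leaked variable can also hide how much the CT features contribute, which is the question the study asks. The Discussion itself argues that waiting for oxygenation to fall means late diagnosis. A model fed an already fallen value would repeat that problem.

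**Working it through.** The plan states no figure on this point, so there is none to reproduce. The check has three steps.

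**1. How each form item could reach a model**

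| Item (section 2.4) | Time stated | Route into the model | Link to the outcome |
|---|---|---|---|
| Arterial blood gases | none | numerical: covered by the normalization sentence in 2.5 | PaO2/FiO2 grades ARDS (2.6) |
| Vasopressor dose | none | numerical: same sentence | may follow onset |
| Ventilator use, vasopressor type | none | categorical: only through the open wording on the last layer in 2.5 | may follow onset |
| ICU and hospital length of stay | whole stay by nature | numerical, but in the outcomes part of the form | known only afterwards |

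**2. Whether another section limits the timing**

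- Section 2.2 excludes patients with PaO2/FiO2 at or below 300 mmHg before admission. This selects patients. It does not say when predictors are measured after admission.
- The sequential definition in 2.2 orders sepsis before ARDS. It does not order predictors before ARDS.
- No section places the CT before onset. The Discussion says that patients at relatively high risk of ARDS are the ones referred for CT, so a scan at or after onset cannot be ruled out.
- Random forest and LASSO (2.7) work on association with the outcome. They tend to favour a leaked variable, not remove it.
- Cross-validation, the 40-patient test group and the 200-patient validating group would share the leak if all use the same form. No other form is described.

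**3. Possible size.** All accuracies below are assumptions.

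For one binary marker, AUC = (sensitivity + specificity)/2.

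- Whole-stay marker such as ventilator use, specificity 0.8: (0.6 + 0.8)/2 = 0.70, and (0.9 + 0.8)/2 = 0.85.
- Lowest PaO2/FiO2 of the whole stay, cut at 300 mmHg: every ARDS grade lies at or below 300, so sensitivity is 1.0 if the diagnostic value is on record. With specificity 0.5 to 0.9, the AUC runs from (1.0 + 0.5)/2 = 0.75 to (1.0 + 0.9)/2 = 0.95.

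To see what such a marker adds to an honest early model, 400,000 patients were simulated. The ARDS rate was 37.5%, the midpoint of the 25–50% in section 2.3. The early score was normal in both groups, with a mean difference of √2·Φ⁻¹(AUC). The marker was independent of the score given the outcome, and the log likelihood ratios were added. Sensitivity of the PaO2/FiO2 marker was set at 0.999.

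| Early model alone | + marker, sens 0.6 / spec 0.7 | + 0.8 / 0.7 | + 0.9 / 0.8 | + PaO2/FiO2, spec 0.5 | + PaO2/FiO2, spec 0.8 |
|---|---|---|---|---|---|
| 0.65 | 0.722 | 0.807 | 0.889 | 0.825 | 0.929 |
| 0.70 | 0.756 | 0.828 | 0.901 | 0.850 | 0.939 |
| 0.75 | 0.789 | 0.849 | 0.914 | 0.874 | 0.949 |

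**The case against.** The strongest reply is that the sentence on numerical variables describes scaling: whatever numerical inputs are used will be normalized. On that reading it does not select predictors. A condensed article may also leave the predictor list and sampling times to a fuller protocol or data dictionary. Admission blood gases would be consistent with the text and with the aim of early prediction.

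Part of this stands. The scaling reading is possible, and a missing variable list alone would be no finding. But section 2.5 describes the input in inclusive terms, keeps the last layer open to other data, and draws on a form that mixes early and late items. Followed as written, it admits the measurements that grade the outcome, and this conflicts with the stated aim.

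Three stronger readings are tempting, and the document does not support them:

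- *Length of stay and death are model inputs.* They sit in the part of the form labelled as outcomes, and nothing says that this part enters the network. Nothing excludes it either, so the plan should say.
- *Ventilator use falls under the sentence on numerical variables.* It is a yes/no item and could enter only through the wording on the last layer.
- *Leaked variables are certain to dominate selection, or ventilator use has no predictive value.* Whether leakage occurs depends on which values are extracted, and the article does not say. Ventilation or vasopressor use that begins before onset is legitimate advance information.

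**Conclusion.** The concern holds as a possibility that the plan leaves open. Neither the network nor the logistic regression and support vector machine models have a prediction time, and neither the CT nor the predictors are required to precede ARDS onset. The case rests mainly on the untimed blood gases, since oxygenation is part of how ARDS is defined and graded. It does not need the length-of-stay items.

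The size cannot be derived from the document. Under the assumptions shown, one whole-stay binary marker alone gives an AUC of 0.70 to 0.85, and a true early AUC of 0.70 could appear as about 0.76 to 0.94. These figures depend on assumed marker accuracy and on independence from the early score. They illustrate and do not forecast. The point touches the primary outcome, and the planned validation would not expose it if all groups use the same form. It should be settled before the models are fitted.

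**What to change.** 1. Define one prediction time for every patient, for example the index CT.
2. Exclude from the analysis patients who already meet the ARDS definition at that time. Anchoring at the CT alone is not enough, because a scan taken after onset would keep the leak.
3. In section 2.5, replace the reference to all numerical variables, and the open wording on the last layer, with a closed list of predictors recorded at or before the prediction time and before ARDS onset.
4. State that the outcomes part of the form, and any ventilator or vasopressor use that starts after the prediction time, are not inputs.
5. Apply the same list to the network and to the logistic regression and support vector machine models in section 2.7.

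The cost is a date and time for each laboratory and treatment item and for ARDS onset, possibly some excluded patients, and an AUC that may be lower but honest.
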